**SAMPLE SIZE CALCULATION**

For the sample size calculation, the parameters of the primary outcome of adherence to LTBI treatment were used. Non-adherence rates vary between studies from 40 to 20%, with most studies being situated between more than 30% abandonment of LTBI treatment. For the sample calculation, we used an expected dropout rate reduction of around 11%. That is, the expected rate of abandonment of the LTBI treatment expected in the 300mg group would be 19% and in the 100mg group, 30%. With a power of 80% to detect differences and a significance level of 5%, it is estimated that 474 subjects are needed in each group. The STATA 15.0 program was used and a loss of 15% was also considered, this number being corrected for 546 study subjects.

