**SELECTION OF INDIVIDUALS AND RANDOMIZATION**

All individuals over 18 years of age with an indication for LTBI treatment between June 01, 2018 and March 30, 2019 at one of the centers selected for the study will be eligible. Individuals whose index case is retreatment, multidrug-resistant and extremely resistant will be excluded, as well as those individuals who were transferred from the original center after two or more weeks of starting treatment in addition to individuals from the prison system.

186 subjects will be included in Espírito Santo and 90 in each of the centers of the

study.

Study subjects will be randomized through a random number worksheet that will contain the treatment regimen in two study groups: Intervention Group: Isonizazide in the 300mg formulation and Control Group: Isonizazide in the 100mg formulation. Randomization will be by block. A randomization list with a random sequence of blocks of participants will be generated for each study center. This strategy ensures that the intervention group and the control group are balanced in terms of the number of participants. To ensure allocation confidentiality, sealed envelopes with the randomization sequence generated using the R software will be sent to each center during the study.

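### The 474 subjects that the protocol says are needed in each group are the total for both groups at its own inputs; the requirement is about 237 to 239 per group

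*Protocol*

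**What the plan says.** The Protocol's Sample Size Calculation bases the trial on abandonment of treatment. It states that "we used an expected dropout rate reduction of around 11" percentage points, with the rate "expected in the 300mg group would be 19% and in the 100mg group, 30" per cent. The operating characteristics are "With a power of 80% to detect differences" and "a significance level of 5" per cent; whether the test is one-sided or two-sided is not said. From these inputs it reports that "it is estimated that 474 subjects are needed in each group". It then adds that "a loss of 15% was also considered, this number being corrected for 546 study subjects".

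Selection of Individuals and Randomization gives the recruitment quotas: "186 subjects will be included in Espírito Santo and 90 in each of the centers of the" study. Research sites and Study design lists five sites, of which Espírito Santo is one. Allocation is by blocks within centre, and the protocol says of it: "This strategy ensures that the intervention group and the control group are balanced in terms of the number of participants". I read that as 1:1.

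**The concern.** The sentence gives a per-group requirement that its own inputs do not produce and that the recruitment quotas cannot meet. If 474 were needed in each arm, the trial would need 948 evaluable participants, yet the quotas add to 546. Both statements cannot be right.

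This sentence is the protocol's only justification of the size of the randomized trial. The Analysis Plan commits the report to CONSORT, so the statement is likely to be carried into publication. A reader who takes it literally would conclude that the trial enrolled little more than half of what it needed, and might dismiss a null result for that reason.

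**Working it through.** **Inputs.** From Sample Size Calculation: p₁ = 0.30 (100 mg), p₂ = 0.19 (300 mg), difference 0.11, power 80% (z = 0.8416), significance 5%. I assume a two-sided test (z = 1.96) because sidedness is not stated. Allocation is 1:1.

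**Step 1: reproduce the stated figure.**

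- Unpooled variance: n = (1.96 + 0.8416)² × (0.30 × 0.70 + 0.19 × 0.81) / 0.11² = 7.849 × 0.3639 / 0.0121 = 236.05, so **237 per group, 474 in total**.
- Pooled variance under the null, which matches Pearson's chi-square in the Analysis Plan: the mean rate is 0.245, and n = [1.96 × √(2 × 0.245 × 0.755) + 0.8416 × √0.3639]² / 0.0121 = 238.8, so **239 per group, 478 in total**.
- Pooled with continuity correction: 257 per group, 514 in total.
- Arcsine: 238 per group.
- One-sided 5%: 186 (unpooled), 188 (pooled) or 206 (with continuity correction) per group.

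None of these variants gives 474 per group. The two-sided unpooled formula gives 474 exactly, as the sum of both groups.

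**Step 2: power at the candidate sizes** (pooled two-sided test, 30% against 19%).

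| Per group | Total | Power |
| --- | --- | --- |
| 237 | 474 | 79.7% |
| 273 | 546 | 85.0% |
| 474 | 948 | 97.7% |

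The stated 80% goes with 474 in total.

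**Step 3: follow the figure through the rest of the plan.**

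- Loss allowance: 474 × 1.15 = 545.1, taken up to 546. This links 474 to 546 but does not by itself show whether they are totals.
- Quotas: 186 + 4 × 90 = 546, or 273 per arm. This takes the 90 to apply to the four sites other than Espírito Santo. Counting a fifth centre of 90 would give 186 + 5 × 90 = 636.
- If 474 were per group, the total would be 948 before losses, and about 1,091 (× 1.15) or 1,116 (÷ 0.85) after them.

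Neither reading of the quotas comes near 948.

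**Step 4: the loss allowance.** Multiplying by 1.15 does not fully offset a 15% loss: 546 × 0.85 = 464.1, ten short of 474, whereas 474 / 0.85 = 557.6, so 558. What this does to power depends on how losses are analysed:

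- Lost participants excluded: 232 per arm, 78.9% power.
- Losses already counted within the 30% and 19%: 273 per arm, 85.0% power.
- A further 15% lost and all counted as failures: the rates become 0.15 + 0.85 × 0.30 = 40.5% and 0.15 + 0.85 × 0.19 = 31.2%. At 273 per arm, power is about 63%.

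**The case against.** The best reply is that this is a slip of wording in a plan whose working numbers are sound. The recruitment target and the centre quotas already treat 474 as the total, and no test, allocation or target changes when the sentence is corrected. That stands, and it limits the point to a false statement of the requirement.

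A second reply is that the sample size paragraph on its own could be read as 474 rising to 546 within each group. It could, and the multiplication by 1.15 does not rule that out. The standard formula and the centre quotas do. The quotas do depend on reading the 90 as applying to four sites, but the alternative total of 636 does not rescue the per-group reading.

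A third reply is that 237 is not the only correct answer. The planned chi-square test points to 239, and 237 per group gives that test 79.7% power. This is fair, and the correction should give both figures. It does not help 474 per group.

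One might also infer from the loss allowance that the trial will have only 79% power. The documents do not support that as a general statement. It holds only if lost participants leave the analysis, and the intention-to-treat population in the Analysis Plan keeps them. The protocol does not say whether the 15% is additional to the abandonment rates or how lost participants' outcomes are counted. The 12-person gap between 546 and 558 is small beside the uncertainty in the assumed rates, since the protocol itself cites non-adherence from 20% to 40%.

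**Conclusion.** The stated per-group requirement is wrong. At the protocol's own inputs, 474 is the total for both groups, and the requirement per group is about 237 (unpooled) or 239 (pooled). The label overstates the requirement by a factor of about two, or 1.84 if a continuity correction is used. The conclusion assumes a two-sided test and 1:1 allocation. A one-sided test would need fewer still, so the missing sidedness does not change it.

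A reader might infer that the trial is recruited to roughly half its need, or is underpowered. The documents do not support this: 546 in total, 273 per arm, exceeds the 474 to 478 that the inputs require and gives 85.0% power before any exclusions. The loss allowance is a minor secondary matter, and its effect on power can be stated only conditionally.

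**What to change.** Replace the sentence with wording such as: *about 237 subjects per group (239 with pooled variance), 474 in total; 546 in total (273 per arm) after the allowance for losses*. State in the same place that the test is two-sided, if that is what was intended.

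If the protocol also reports power after losses, it should say that 546 leaves about 464 participants and 79% power only when lost participants are excluded, which is not the intention-to-treat population it defines. Otherwise leave that figure out.

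The cost is one corrected sentence. No extra participants are needed, and the centre quotas do not change.

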**SELECTION OF HEALTH FACILITIES**

The health facilities will be selected among primary health care facilities, Family Health Strategy facilities and Reference Centers for the treatment of TB. All health facilities in the study areas will be identified. Your selection will be made according to the number of individuals who underwent treatment for LTBI in the previous year in each capital.

**SELECTION OF INDIVIDUALS AND RANDOMIZATION**

All individuals over 18 years of age with an indication for LTBI treatment between June 01, 2018 and March 30, 2019 at one of the centers selected for the study will be eligible. Individuals whose index case is retreatment, multidrug-resistant and extremely resistant will be excluded, as well as those individuals who were transferred from the original center after two or more weeks of starting treatment in addition to individuals from the prison system.

186 subjects will be included in Espírito Santo and 90 in each of the centers of the

study.

Study subjects will be randomized through a random number worksheet that will contain the treatment regimen in two study groups: Intervention Group: Isonizazide in the 300mg formulation and Control Group: Isonizazide in the 100mg formulation. Randomization will be by block. A randomization list with a random sequence of blocks of participants will be generated for each study center. This strategy ensures that the intervention group and the control group are balanced in terms of the number of participants. To ensure allocation confidentiality, sealed envelopes with the randomization sequence generated using the R software will be sent to each center during the study.

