# METHODS

STUDY STEPS

First step

Research sites and Study design

This step will be carried out in Brasília, Curitiba, Santa Catarina, Ribeirão Preto, Espírito Santo in the form of a pragmatic, open-label, randomized clinical trial in health units that provide care to patients with Tuberculosis and whether or not they have a Tuberculosis Control Program (PCT acronym in Portuguese). ). The health facilities that prescribe LTBI treatment will be chosen. From June 2018 to March 2019, people over 18 years of age with indication for LTBI treatment will be invited to participate in this study.

After signing the informed consent term, the contacts will be randomized to receive Isoniazid 100mg or 300mg and will be followed up until the end of treatment.

The primary outcome will be the success rate of LTBI treatment in the new 300mg formulation represented by the proportion of subjects with 270 doses of isoniazid between 9 to 12 months.

Secondary outcomes will be evaluated by comparing adverse effects in the two groups (Isoniazid 100mg or 300mg).

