**ANALYSIS PLAN**

The explanatory variable of primary interest will be the participant's adherence to LTBI treatment. Other explanatory variables will be used in the analysis models, respecting possible hierarchy and confounding relationships: (1) Demographic and socioeconomic factors: age, sex, place of residence, state capital (yes/no), year of diagnosis, ethnicity or skin color (white, black, brown, yellow and indigenous), formal education (number of school years completed); (2) Pre-existing medical conditions and comorbidities: HIV serology, diabetes, alcoholism and mental illness; (3) Variables associated with infection or adverse effects of LTBI treatment.

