LTBI treatment success and dropout rates will be calculated for each study group. Student's t test will be used to compare means and Pearson's chi-square test will be used to compare proportions and the variables associated with the outcome of interest (p < 0.20) will be included in the multivariate regression model for adjustment. Results are presented in relative risk (RR) with a 95% confidence interval (95% CI). Ideally, all subjects included in the study should complete it following the initial protocol. This situation almost never happens, for different reasons. In general, there are losses, non-adherence to treatments and other deviations from the protocol. For the analysis of the results, two basic populations will be defined: the first is defined by the “intention-to-treat” (ITT) which will include all patients regardless of protocol violations and loss to follow-up; the second, referred to as “per-protocol” (PP), will be a subset of the first, including only patients who completed treatment according to the protocol criteria, excluding all violators. These two analyzes are important, as a significant violation of the criteria established in the protocol (many losses, switching or poor adherence to treatment, and/or other deviations) in the ITT analysis may include a no-difference bias resulting in a lower treatment effect and greater risk of falsely declaring non-inferiority. On the other hand, the PP analysis, in these adverse situations, may include a difference bias, resulting in a greater effect of the treatments and a greater risk of falsely declaring superiority. Therefore, ITT analyzes are conservative for superiority while PP are conservative for non-inferiority. We will therefore present both and the CONSORT Statement will also be used throughout the report (Schulz, Altman and Moher, 2010). All analyzes will be performed in Stata, version 15.0.

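### Randomisation is blocked separately in each centre, but centre has no place in the stated analysis; the test is slightly conservative and the fix is free.

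*Protocol*

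**What the plan says.** - **Allocation** (Protocol, Selection of Individuals and Randomization). Randomisation is in blocks, with one list per centre: "A randomization list with a random sequence of blocks of participants will be generated for each study center". The stated purpose is equal arm sizes: "This strategy ensures that the intervention group and the control group are balanced in terms of the number of participants". Recruitment targets are 186 in Espírito Santo and 90 in each other centre.
- **Outcome** (Protocol, Methods, first step). The primary outcome is binary: the "proportion of subjects with 270 doses of isoniazid between 9 to 12 months".
- **Test** (Protocol, Analysis Plan). "Pearson's chi-square test will be used to compare proportions". No stratification is mentioned and no other test for proportions is named for the trial. Results are to be given as relative risks with 95% CI.
- **Adjustment** (same section). Covariates are chosen from the data: "the variables associated with the outcome of interest (p < 0.20) will be included in the multivariate regression model for adjustment". The candidates closest to centre are in the first group: "Demographic and socioeconomic factors: age, sex, place of residence, state capital (yes/no), year of diagnosis". The other two groups cover comorbidities and variables linked to infection or adverse effects. Study centre appears in none of the three.

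**The concern.** One blocked list per centre makes centre a stratification factor, whether or not the protocol uses that word. Allocation is balanced inside each centre, so differences between centres in completion largely cancel out of the comparison of arms. An unstratified test does not know this. It counts those differences as noise, so its standard error is larger than the design warrants.

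The covariate rule does not repair this. State capital has two levels and cannot stand for five centres. Place of residence describes the patient, its coding is not defined, and it enters only if it passes the screen.

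Centre differences are plausible. The Introduction says dispensing differs between services, and facilities range from primary care units to TB reference centres. What is at stake is some precision and power, and a main analysis that matches the allocation.

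**Working it through.** **Inputs.** Centre targets come from Selection of Individuals and Randomization. The 30% and 19% abandonment rates, the 474, the 15% loss, the 546 and the 20-40% range between studies come from Sample Size Calculation. As that section does, abandonment is treated as the complement of success; the test is symmetric in the two.

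**Step 1: what a centre is.** 186 + 4 x 90 = 546, and 474 x 1.15 = 545.1, which rounds up to the planned 546. The targets add up only if there are five centres, and the second-stage Data collect section also speaks of five. Weights are 186/546 = 0.341 for Espírito Santo and 90/546 = 0.165 for each other centre. The 474 is worded as a per-group number but is used here as a total, since that is how it leads to 546.

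**Step 2: share of outcome variance due to centre.** Share = Σ w(p_c − p̄)² / [p̄(1 − p̄)]. No centre rates are given, so the spreads are assumptions, with Espírito Santo at 30% in each.

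- 20-40% (others 20, 25, 35, 40): 0.1648 x (0.10² + 0.05² + 0.05² + 0.10²) = 0.00412. Divided by 0.30 x 0.70 = 0.21, this is 2.0%. Divided by 0.245 x 0.755 = 0.185 (the mean of 30% and 19%), it is 2.2%.
- The same five rates with Espírito Santo at 20%: mean = 0.3407 x 0.20 + 0.1648 x 1.30 = 0.2824. The sum is 0.3407 x 0.0824² + 0.1648 x (0.0324² + 0.0176² + 0.0676² + 0.1176²) = 0.00557. Divided by 0.185, this is 3.0%. The range is therefore about 2-3%.
- 15-45% (others 15, 22, 38, 45): 0.1648 x 0.0578 = 0.00953; divided by 0.21, this is 4.5%.
- 10-60% (others 10, 15, 35, 60): 0.1648 x 0.155 = 0.0255; divided by 0.21, this is 12.2%.

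**Step 3: effect on the unstratified test, in closed form.** With 1:1 allocation inside each centre and no treatment effect, the true variance of the arm difference is (1 − share) times the variance the unstratified test uses. Type I error is then 2[1 − Φ(1.96/√(1 − share))].

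- 20-40%: 1.96/√0.9804 = 1.980, giving 4.8%; standard error about 1% too large.
- 15-45%: 1.96/√0.9546 = 2.006, giving 4.5%; about 2.4% too large.
- 10-60%: 1.96/√0.8783 = 2.091, giving 3.7%; about 6.7% too large.

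**Step 4: simulation.** 100,000 runs, N = 546, 1:1 in each centre, average rates 30% v 19%, common odds ratio across centres. Each cell gives the unstratified chi-square, then Cochran-Mantel-Haenszel stratified by centre.

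| Control abandonment across centres | Type I error | Power | Power lost |
| --- | --- | --- | --- |
| equal | 5.2% v 5.1% | 85.1% v 85.0% | none |
| 20-40% | 4.9% v 5.1% | 85.5% v 85.8% | 0.3 points |
| 15-45% | 4.5% v 5.0% | 86.1% v 86.9% | 0.8 points |
| 10-60% | 3.5% v 4.9% | 86.7% v 89.0% | 2.3 points |

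Simulation error on the type I figures is about √(0.05 x 0.95/100,000) = 0.07 points, so they agree with Step 3 to within about 0.2 points. At N = 474 the losses are about 0, 0.5, 1.1 and 3.0 points.

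**The case against.** Four points can be made for the plan.

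1. **The effect is small and in the safe direction.** This stands. It limits the point to efficiency and good practice.
2. **The chi-square is never called the primary test.** This also stands. The same sentence goes on to a regression for adjustment, so the headline estimate might be an adjusted relative risk. But centre is not a candidate for that regression either, so neither route uses the strata.
3. **Place of residence may stand in for centre.** If it were coded by study area, it would usually pass a p < 0.20 screen whenever centres differ enough to matter. This stands only in part, because the protocol does not define the coding and still leaves entry to the data.
4. **Handling of centre belongs in the SAP.** That would settle the matter had the protocol been silent. It is not: it fixes the test, the candidate list and the selection rule.

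A reader might infer more than the documents support:

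- **That the trial throws its stratification away, or that the p-value is invalid.** The stated purpose of the lists is balance in numbers, and that balance survives any analysis. The error makes false positives slightly rarer.
- **That the loss is worth dozens of participants.** A standard deviation of 15 points between centres would make centre explain about 10% of variance, or roughly 55 of 546 participants. But within a 20-40% range the standard deviation cannot exceed 10 points, half the range, and then only with centres split between the two extremes. Nothing in the protocol points to a wider spread.

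**Conclusion.** The point holds as a modest matter of efficiency and consistency. Allocation is stratified by centre, while the stated test ignores centre and the stated covariate rule leaves it out. There is no bias and no inflation of type I error.

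At N = 546, a 20-40% spread in centre abandonment loses about 0.3 points of power, with type I error near 4.8-4.9%. A 15-45% spread loses about 0.8 points. It takes a spread as wide as 10-60% to lose 2-3 points (2.3 at N = 546, 3.0 at N = 474).

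These sizes rest on assumed centre rates, five centres, 1:1 allocation within each and a common odds ratio. The textual mismatch does not depend on them. The reading of five centres is well supported by the recruitment targets, but the randomisation section also speaks of patients attending centres selected for the study, which could mean individual health units.

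**What to change.** In the Analysis Plan, state that the main comparison of treatment success is a Mantel-Haenszel relative risk with 95% CI, stratified by randomisation centre. Equally acceptable is a relative-risk regression in which centre is always included and is exempt from the p < 0.20 screen. Keep the unstratified chi-square as a sensitivity analysis.

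Also say what a centre is. If it means the five study areas, strata of 90 or more present no difficulty for either method. If lists are made for individual health units, strata are smaller, and Mantel-Haenszel or a random centre effect is the better choice.

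The cost is one or two sentences. The effect measure, the software and the sample size stay as they are.

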**ANALYSIS PLAN**

The explanatory variable of primary interest will be the participant's adherence to LTBI treatment. Other explanatory variables will be used in the analysis models, respecting possible hierarchy and confounding relationships: (1) Demographic and socioeconomic factors: age, sex, place of residence, state capital (yes/no), year of diagnosis, ethnicity or skin color (white, black, brown, yellow and indigenous), formal education (number of school years completed); (2) Pre-existing medical conditions and comorbidities: HIV serology, diabetes, alcoholism and mental illness; (3) Variables associated with infection or adverse effects of LTBI treatment.

LTBI treatment success and dropout rates will be calculated for each study group. Student's t test will be used to compare means and Pearson's chi-square test will be used to compare proportions and the variables associated with the outcome of interest (p < 0.20) will be included in the multivariate regression model for adjustment. Results are presented in relative risk (RR) with a 95% confidence interval (95% CI). Ideally, all subjects included in the study should complete it following the initial protocol. This situation almost never happens, for different reasons. In general, there are losses, non-adherence to treatments and other deviations from the protocol. For the analysis of the results, two basic populations will be defined: the first is defined by the “intention-to-treat” (ITT) which will include all patients regardless of protocol violations and loss to follow-up; the second, referred to as “per-protocol” (PP), will be a subset of the first, including only patients who completed treatment according to the protocol criteria, excluding all violators. These two analyzes are important, as a significant violation of the criteria established in the protocol (many losses, switching or poor adherence to treatment, and/or other deviations) in the ITT analysis may include a no-difference bias resulting in a lower treatment effect and greater risk of falsely declaring non-inferiority. On the other hand, the PP analysis, in these adverse situations, may include a difference bias, resulting in a greater effect of the treatments and a greater risk of falsely declaring superiority. Therefore, ITT analyzes are conservative for superiority while PP are conservative for non-inferiority. We will therefore present both and the CONSORT Statement will also be used throughout the report (Schulz, Altman and Moher, 2010). All analyzes will be performed in Stata, version 15.0.

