**Phase 2- Follow-up**

Study subjects will be interviewed by the researchers regarding medication intake and adverse effects at the following study periods: week 2, first month, second month, and end of treatment.

Thus, 2 forms will be built, one for diagnosis and another for follow-up (Appendix 1 and 2), based on the forms proposed by the PNCT for the follow-up of these people, already in use in other capitals. The follow-up will also be entered into the notification system for the treatment of latent tuberculosis infection in force in each municipality. The forms will include sociodemographic and clinical information regarding initiation, follow-up and outcome of LTBI treatment. The data can be collected independently in the presence of a data network, whether on cell phones, tablets, notebooks or desktops, if necessary, the data can also be collected in physical media.

In secondary outcomes, in addition, new technologies are being proposed so that the treatment of LTBI can be monitored by health services and so that the health education process, especially applied to TB, can be more easily achieved through an application.

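### The planned covariate adjustment can admit adverse effects, a post-randomisation secondary outcome, so the adjusted RR need not estimate the total effect of assignment to 300mg or 100mg

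*Protocol*

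**What the plan says.** The ANALYSIS PLAN section of the Protocol opens with the model variables: "Other explanatory variables will be used in the analysis models, respecting possible hierarchy and confounding relationships". Three groups follow: demographic and socioeconomic factors, pre-existing conditions, and "3) Variables associated with infection or adverse effects of LTBI treatment".

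The same section then gives the selection rule: "the variables associated with the outcome of interest (p < 0.20) will be included in the multivariate regression model for adjustment". The next sentence says that results will be reported as relative risks with 95% confidence intervals. The section also has success and dropout rates calculated for each study group, with Pearson's chi-square test for proportions, and it defines intention-to-treat and per-protocol populations. It does not say whether the unadjusted or the adjusted result is primary.

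Two other places fix the status of adverse effects. METHODS, First step: "Secondary outcomes will be evaluated by comparing adverse effects in the two groups". Phase 2 - Follow-up: participants are "interviewed by the researchers regarding medication intake and adverse effects at the following study periods: week 2, first month, second month, and end of treatment". The primary outcome, in METHODS, First step, is completion of 270 doses within 9 to 12 months.

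**The concern.** Adverse effects are recorded from week 2 onwards, so the formulation a participant was assigned can influence them. They are also an obvious reason not to reach 270 doses. A variable that lies between assignment and outcome is a mediator. Adjusting for it removes whatever part of the formulation's effect acts through tolerability. It can also introduce bias if some unmeasured factor causes both adverse effects and stopping.

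This route is not remote in this trial. The first item under OBJECTIVE is serious or unexpected reactions with 300mg. The INTRODUCTION warns of the harm from overdose, and the Subanalysis section foresees participants confusing the two tablet strengths in either direction. If such errors change tolerability in one arm, that belongs in the effect of the formulation on completion. Adjustment for adverse effects takes it out, and where 300mg is less well tolerated it makes 300mg look better than it is.

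**Working it through.** **Step 1. Do the passages combine as feared?** Group (3) of the covariate list names adverse effects. The selection rule is association with the outcome at p < 0.20. METHODS and Phase 2 - Follow-up make adverse effects a post-randomisation outcome. No sentence limits adjustment to baseline variables. So a team following the text could condition the arm comparison on adverse effects.

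**Step 2. Inputs.** From SAMPLE SIZE CALCULATION: expected dropout of 19% (300mg) and 30% (100mg). The total effect on the dropout scale is therefore 0.19 / 0.30 = 0.633, and values below 1 favour 300mg. The Protocol gives no adverse-effect rates and no figure for how strongly they drive stopping. Both are assumptions here, varied over a range.

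**Step 3. Formula.** Let *a* be the proportion with an adverse effect in an arm, *k* the risk ratio for dropout with versus without an adverse effect (the same in both arms), and *b* the dropout risk without one. Then:

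- dropout in an arm = *b* × [1 + (*k* − 1)*a*];
- the part of the RR that acts through adverse effects is M = [1 + (*k* − 1)*a*(300mg)] / [1 + (*k* − 1)*a*(100mg)];
- the adverse-effect-adjusted RR = 0.633 / M.

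This assumes a correctly specified ratio model and no unmeasured common cause of adverse effects and stopping.

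**Step 4. Results.**

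| Adverse effects, 100mg vs 300mg | *k* | M | Adjusted RR | Share of log RR removed |
|---|---|---|---|---|
| 20% vs 20% | 3 | 1.4/1.4 = 1.000 | 0.633 | 0% |
| 30% vs 20% | 2 | 1.2/1.3 = 0.923 | 0.686 | 18% |
| 30% vs 20% | 3 | 1.4/1.6 = 0.875 | 0.724 | 29% |
| 30% vs 15% | 3 | 1.3/1.6 = 0.813 | 0.779 | 45% |
| 40% vs 20% | 3 | 1.4/1.8 = 0.778 | 0.814 | 55% |
| 20% vs 30% | 3 | 1.6/1.4 = 1.143 | 0.554 | −29% (effect exaggerated) |

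**Step 5. Would the screen let adverse effects in?** Each row was simulated 4,000 times with 237 participants per arm, testing adverse effects against dropout at p < 0.20. The figure of 237 takes the Protocol's 474 as a total. That reading fits its 546, which is 474 × 1.15 = 545.1 rounded up, and also 186 + 4 × 90 from the centre allocation. Adverse effects passed the screen in at least 99.9% of simulated trials in every row. With *k* at 2 or 3, admission is close to certain.

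**The case against.** Four points on the other side carry weight.

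- **The hierarchy and confounding clause.** A mediator is not a confounder, so a careful analyst could read the clause as keeping adverse effects out. It is a partial safeguard. But it bars no named variable or class of variable, the list it introduces includes adverse effects, and the only operative rule given is p < 0.20.
- **Loose wording.** Group (3) could mean predictors of adverse effects rather than the effects themselves. The passage also names adherence, not arm, as its main explanatory variable, so the list may have been written with a predictors-of-adherence model in mind, where adverse effects would be legitimate. Nothing separates such a model from the one used for adjustment, and the RR sentence follows directly on the adjustment sentence.
- **The unadjusted comparison.** The per-arm rates and chi-square test do not involve covariates and stand as they are. A reader might infer that the trial's only estimate is compromised; the text does not support that. What is true is that neither estimate is named as primary.
- **Bioequivalence.** The INTRODUCTION reports the two formulations as bioequivalent, so similar adverse-effect rates are plausible, and with equal rates the adjusted RR does not move. Bioequivalence does not cover the tablet-confusion errors that the Subanalysis section foresees, so a difference cannot be ruled out.

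Two stronger readings are tempting and should be resisted. One is that adjustment would wipe out the whole treatment effect. That follows only if the formulation is assumed to act on completion through adverse effects alone, which the documents nowhere say. The other is that the p < 0.20 screen by itself biases the comparison. Of the 11 listed baseline variables, 11 × 0.20 = 2.2 would enter by chance if all were unrelated to the outcome and independent, but admitting irrelevant baseline covariates in a randomised comparison is not shown to bias it. The fault in the screen is that the data choose the model behind the RR and that it has no bar on post-randomisation variables.

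**Conclusion.** The point holds as a defect of specification. Read plainly, the ANALYSIS PLAN allows a secondary outcome that arises after randomisation into the adjusted RR for 300mg versus 100mg, under a rule it would very likely pass.

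The consequence depends on whether adverse-effect rates differ by arm. At the planned dropout rates the RR of 0.633 becomes 0.69 to 0.81 in the cases where 300mg has fewer adverse effects (18% to 55% of the log RR removed), becomes 0.55 in the case where it has more (30% versus 20%, *k* = 3), and does not change where rates are equal. These sizes are illustrations that rest on assumed adverse-effect rates and an assumed *k* of 2 or 3; they are not predictions. The direction is not fixed either. A reader might infer that the adjustment always dilutes the effect, but it can also exaggerate it.

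**What to change.** For the comparison of arms:

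1. Remove adverse effects, and any other variable measured after randomisation, from the adjustment list.
2. Replace the p < 0.20 screen with a small set of baseline covariates, for example age, sex and HIV status, which are already listed. Add centre, because the randomisation lists are generated per centre.
3. Fix that set before any outcome data by arm are examined. The trial is open-label, so waiting until the database is locked would let accruing results guide the choice.
4. State whether the unadjusted or the adjusted estimate is primary.

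Keep adverse effects as an outcome compared between arms. Keep the p < 0.20 model, with adverse effects if wanted, only as a separate exploratory analysis of predictors of abandonment.

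The cost is a change of wording and no new data. The downside is that some listed covariates leave the main model.
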